**Fig. 4 Fig4:**
[figure not shown]
Schedule of enrolment, interventions, and assessments

Participants will be recruited via targeted Facebook ads, the project’s website and through promotion in the regional and national media. Interested participants will be invited to visit the intervention public page (medstres.pl) and watch a short video clip in which the project’s team explains the purpose and scope of the study. Subsequently, they will be asked to declare whether they are at least 18 years old, represent medical professions, and have access to an Internet-connected device; all in order to check whether they are eligible to participate. Upon registration, participants will be asked to provide informed consent. All registration procedures will be conducted online, with no contact from the research team. The implications of participation in the study will be clearly explained in the materials (text and a video clip) on the public website and in the informed consent document. This process was approved by the research ethics committee. After accepting to be randomized to one of four study conditions, participants will be asked to fill out the baseline questionnaires (pretest). Once those are completed, participants will be randomized and allocated with a 1:1:1:1 ratio to one of four study conditions. The registration process is continuous, which means that access to the Med-Stress program is given instantly, but the content is released on Mondays. Every week a new exercise is available and participants will be notified via e-mail. Such a recurrent design is determined by the task that requires participants in three conditions (those that include a perceived social support enhancement module) to take part in a forum discussion at the same time. Depending on the study condition, the intervention will take 3 weeks (active control conditions) or 6 weeks (experimental conditions). Participants will not be informed about the result of the allocation but it is public knowledge that Med-Stress consists of four variants that differ in terms of length (depending on whether a given variant contains one or two modules) and the type of exercises. Regardless of the condition, all participants have access to four optional modules throughout the study: Relaxation, Mindfulness, Cognitive Restructuring, and Lifestyle. Participants will be asked to fill out questionnaires at four times during the study: before the intervention, posttest (i.e., right after the intervention: at 3 or 6 weeks depending on the study condition), and at 6-month and 12-month follow up. Additionally, users assigned to experimental conditions will undergo mid-intervention assessment. Depending on the first module, perceived social support (one scale) or self-efficacy (two scales: self-efficacy to manage job stress and burnout, and self-efficacy to obtain social support) will be measured. At each assessment point, participants will receive an e-mail notification containing a link to the survey. All measurements throughout the study will be obtained online, which has been shown to be a reliable mode of administering psychological, self-report questionnaires [45]. To ensure a high response rate, each e-mail notification will be followed by two reminders every 2 days. Moreover, we will include supportive messages in the survey between questionnaires, thanking the participants for getting this far and encouraging them to continue until completion. All participants will be advised that should they experience any psychological discomfort, harm, or other unintended effects of the intervention or study, they are encouraged to contact the study team or other mental-health professionals. At any time during the intervention period and after completing the program, the participants have the right to withdraw their participation without the obligation to provide their reasons, as stated in the informed consent.

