
### Intervention: Med-Stress

Med-Stress is an unguided open access, standalone Internet-based intervention that consists of four conditions: two experimental and two active controls, to which participants will be randomly assigned. In the experimental conditions, participants will complete two obligatory modules (enhancing self-efficacy and perceived social support or perceived social support and self-efficacy), whereas in the active control conditions they will complete only one of them (enhancing self-efficacy or perceived social support). Each module contains three evidence-based, CBT-framed exercises. Therefore, participants in the experimental conditions will be offered six exercises spaced out over 6 weeks, while the participants in the active controls will be presented with three exercises over the span of 3 weeks. Each exercise will be released once a week and users can work on them at their own pace. Participants will be encouraged to do all tasks, but the new exercise will be made available regardless of the completion of the previous one. Each exercise in each module is preceded with a psychoeducation part delivered via a short, animated movie. Participants will not need to watch the movies in order to complete the exercises, they will be only encouraged to do so. Completion of each model - defined as watching the movie, reading the instructions, and providing written responses online - takes about 1.5 h of screen time per week. Some of the exercises (i.e., *vicarious experience and action planning*) require performing actions away from the computer - in their work environment - and one exercise (*social skills and peer support*) necessitates longer screen time to take part in the forum discussion. Additionally, participants will have the option of benefitting from four additional modules at any time during the intervention.

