#### Active control condition: self-efficacy enhancement module

In this active control condition participants will only be presented with the SE module comprising the same three evidence-based, CBT-framed exercises as in the experimental conditions. Participants will also have access to the same four optional modules. This condition only takes 3 weeks, with one exercise being released each week.

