##### Mindfulness

This module consists of four voice-guided or text-guided exercises: (1) how do body and mind react to thoughts? (2) body scanning, (3) breathing and sounds, and (4) being mindful of emotions. All exercises are designed to strengthen attention, body, thoughts, and emotional awareness to reduce perceived stress. Again, participants can do any chosen number of these exercises throughout the intervention.

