### Statistical analysis

We will conduct analyses of covariance (ANCOVA) with condition assignment as a factor, all primary and secondary measures at posttest as outcomes, and their pretest values as covariates. This will allow us to test for group differences between study conditions posttest while controlling for change over time. ANCOVA has been shown to be more parsimonious than analysis of variance (ANOVA) in randomized trials with a repeated measures design, and thus to have more power [56]. In terms of specific analyses, primarily, we will compare the effects of experimental conditions to each active control to test whether a two-module intervention is more effective that a single-module one. Next, we will compare the effects of the two experimental conditions to check if the sequence of the modules contributes to the intervention effects. Bonferroni’s adjustment for multiple comparisons (five comparisons and five outcomes) will be applied, which will lower the *p* levels to .002 for detection of the effects. Additionally, we will conduct separate ANCOVA to test whether the differences in outcomes between study conditions are maintained at the 6-month and 12-month follow up. Furthermore, we will conduct mediation analyses to verify the hypothesized mechanism of the effect of condition assignment on the primary and secondary outcomes. Sequential mediation analyses will be applied using the PROCESS macro [57] with condition assignment as a predictor, primary and secondary measures posttest as the outcomes, their baseline scores as covariates, and self-efficacy and perceived social support posttest as mediators (see Figs. 1 and 2 for conceptual models of mediations).

Additionally, we will carry out moderation analysis to test whether the initial (pre-intervention) expectancy about the positive outcomes of the treatment (i.e., how successful the intervention would be in reducing stress and burnout symptoms in participants’ opinions) moderates the relationship between the condition assignment and the study outcomes. As participants in the study will have the option of engaging in one or more out of four additional modules, we will consider participation in them as a control variable.

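### Use of the optional modules, self-chosen after randomisation, is planned as a control variable with no model named and the primary ANCOVA not excluded

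*Protocol article*

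**What the plan says.** All from the protocol article.

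- **Allocation** (Procedure): "Once those are completed, participants will be randomized and allocated with a 1:1:1:1 ratio to one of four study conditions". The step that precedes this is the baseline questionnaire.
- **Access to the optional modules** (Procedure): "Regardless of the condition, all participants have access to four optional modules throughout the study". The Intervention section gives a narrower window: "participants will have the option of benefitting from four additional modules at any time during the intervention". Use is voluntary under both.
- **Time to posttest** (Procedure): posttest falls "right after the intervention: at 3 or 6 weeks depending on the study condition". The active controls have the shorter period and the experimental conditions the longer one.
- **Purpose of the modules** (Optional modules): the mindfulness exercises are meant to strengthen attention and "emotional awareness to reduce perceived stress", and the lifestyle module is also aimed at lowering stress. The primary stress outcome is the PSS-14, a perceived-stress scale.
- **Named covariates** (Statistical analysis): the ANCOVA lists pretest values, and the mediation models list baseline scores.
- **Optional modules in the analysis** (Statistical analysis, end of the paragraph on expectancy as a moderator): "we will consider participation in them as a control variable". The reason given is only that participants may choose to use the modules. No model is named, and the adjustment is not called a sensitivity or exploratory analysis.

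**The concern.** A covariate in a randomised comparison is safe if assignment cannot have affected it. Baseline scores meet that condition; module use does not. It happens after allocation, by choice, and over a period whose length depends on the arm.

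Two things can go wrong if it enters the model.

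1. If being in a 6-week condition leads to more module use, and the modules lower stress as intended, part of the effect of assignment runs through that use. Adjustment removes this part.
2. Users and non-users probably differ in motivation or current stress, which also predict the outcome. If uptake differs by arm, comparing arms within levels of use compares people who differ on these unmeasured traits, even when neither assignment nor the modules do anything.

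Four of the five planned comparisons set a 6-week arm against a 3-week arm, and the plan treats these four as its main test.

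**Working it through.** **Is the variable affected by assignment?** Setting the sections side by side, randomisation comes first and module use follows. The window before posttest is 6 weeks against 3, a ratio of 2, in the four experimental-versus-control contrasts. This is so whether access lasts for the study or only for the intervention. In the fifth contrast, between the two experimental conditions, both windows are 6 weeks.

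**Inputs for size.** The documents give no uptake rates, no module effect and no link between motivation and outcome. All of these are assumed: uptake 30% in a 3-week arm and 40, 50 or 60% in a 6-week arm; pre-post correlation 0.5; within-arm posttest SD of 1; and an unmeasured trait with loading *g* = 0.3 or 0.5 on both the tendency to use modules and (as lower stress) the outcome.

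**Bias from the unmeasured trait, inert modules.** In the adjusted model the coefficient on use has size *g*² × *m*/*v*. Here *m* is the mean over the two arms of the normal density at the uptake threshold, and *v* is the mean over the arms of *p*(1 − *p*). The bias in the arm contrast is that coefficient times the difference in uptake.

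Worked case, 30% v 50%, *g* = 0.5:
- *m* = (0.3477 + 0.3989)/2 = 0.3733
- *v* = (0.21 + 0.25)/2 = 0.23
- coefficient = 0.25 × 0.3733/0.23 = 0.406
- bias = 0.406 × 0.20 = 0.081 SD

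The simulation (1,000,000 participants per scenario, no true effect) agrees. For 40% and 60% the density is 0.3863 and *v* = 0.225.

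| Uptake (3-wk v 6-wk arm) | *g* | Formula | Simulated, adjusted | Simulated, unadjusted |
|---|---|---|---|---|
| 40% v 40% | 0.5 | 0.000 | 0.002 | 0.002 |
| 30% v 40% | 0.3 | 0.015 | 0.011 | −0.004 |
| 30% v 40% | 0.5 | 0.041 | 0.040 | 0.000 |
| 30% v 50% | 0.3 | 0.029 | 0.027 | −0.002 |
| 30% v 50% | 0.5 | 0.081 | 0.082 | 0.001 |
| 30% v 60% | 0.3 | 0.044 | 0.044 | 0.001 |
| 30% v 60% | 0.5 | 0.122 | 0.127 | 0.005 |

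Positive values count against the experimental arm. With a true effect of 0.20 SD and inert modules, the adjusted estimate ran from 0.185 (30% v 40%, *g* = 0.3) down to 0.079 (30% v 60%, *g* = 0.5). The unadjusted estimate stayed at about 0.20.

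**A second simulation**, with a log-odds model for uptake (0.5 to 0.75 per SD of the trait) and an outcome loading of 0.3 to 0.5 SD, gave a bias of 0.014 to 0.03 SD at 31% v 41% and 0.03 to 0.065 SD at 31% v 51%. The unadjusted ANCOVA was again unbiased.

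**Effect removed through module use.** Suppose the modules lower stress by 0.20 SD, the direct effect is 0.20, and there is no unmeasured trait. The part acting through use is 0.20 × the uptake difference: 0.02, 0.04 or 0.06 for differences of 0.10, 0.20 or 0.30. The total effect is then 0.22, 0.24 or 0.26. Simulated unadjusted estimates were 0.219, 0.237 and 0.257; adjusted ones were 0.197 to 0.199.

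**Direction.** The table assumes that the trait raises uptake and lowers stress, as motivation might. If more stressed people use the modules more and still end with higher scores, the sign reverses and the bias favours the experimental arm.

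**The case against.** The strongest reply is that the primary model is already specified correctly. The ANCOVA and the mediation models each have a covariate list, module use is in neither, and the sentence in dispute comes after the moderation analysis and says only that the variable will be considered. That is a fair reading, and it rules out saying that the plan definitely adjusts its primary ANCOVA for module use. It does not settle the matter. The reason given is general and has nothing to do with expectancy, no model is excluded, and a covariate of this kind is a poor choice in the moderation model too.

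A reader might also infer more than the documents support on these points:

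- *Uptake differs by arm.* Nothing says so. Access is the same for all; the difference is inferred from the 3- and 6-week windows. With equal uptake the linear model shows no bias.
- *Every contrast is affected.* The duration argument does not reach the comparison of the two experimental conditions. It is also weaker at 6 and 12 months if access lasts throughout the study.
- *The analysis stops being intention-to-treat.* The analysis set is still all randomised participants. What changes is the quantity estimated.
- *False positives become common.* With 300 per arm and a pre-post correlation of 0.5, the standard error is √(2 × 0.75/300) = 0.071 SD. A bias of 0.065 is 0.92 standard errors, against a critical value of 3.09 at α = 0.002. The false-positive rate is then about 1.5%: above the nominal 0.2%, but low. Even the extreme 0.122 SD gives about 9%.

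That the unshown analysis plan may name the model does not dispose of the point, because the protocol itself states the choice.

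**Conclusion.** The point holds in a limited form. The protocol commits to a post-randomisation, self-selected control variable without saying where it applies, and leaves it open to enter the primary ANCOVA. Wherever it enters, the contrast is no longer the effect of assignment to two modules rather than one.

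The size cannot be found from the documents. Under the assumptions above it is about 0.01 to 0.07 SD in one simulation and up to 0.12 to 0.13 SD in the most extreme case of the other, beside a planning effect given as 0.20. It is zero if uptake is equal across arms. The sign is not known in advance, so the adjustment cannot be defended as conservative. The structural argument is firm; the differential uptake on which any bias depends is a plausible inference for four of the five contrasts, not a stated fact.

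**What to change.** Remove the control-variable sentence. State instead that the posttest ANCOVA, the follow-up ANCOVAs, the moderation models and the mediation models adjust for pre-randomisation covariates only. Report use of each optional module by arm as a descriptive table. If the role of module use is of interest, analyse it separately, label that analysis exploratory, and state its causal assumptions.

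The cost is one replaced sentence and one descriptive table. The sample size (607 before dropout, 1200 planned) and the 0.002 threshold do not change.

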### Sample size

The study will be conducted among professionally active health professionals at risk of job stress and burnout. Bonferroni’s adjustment for multiple comparisons will be applied: there will be a comparison between the two experimental conditions and between each experimental condition and each active control condition giving a total of five comparisons posttest. Furthermore, we will include five outcomes. Taken together, this will lower *p* levels to .002. Meta-analyses of the effectiveness of web-based interventions for stress reduction found a small effect of *g* = 0.30 [19] for work-related stress, and a medium size effect of *d* = 0.49 for general stress [43]. Taking into account the minimum effect size of *d* = 0.20, in analysis of covariance (ANCOVA) with a significance level of α = 0.002, statistical power of 0.90, and the number of conditions (two experimental conditions and two active controls), a total of 607 participants will be set (152 participants per condition). Furthermore, a high dropout rate is usually encountered in unguided interventions (between 5 and 45%; [44]) and thus we ultimately plan for a sample of 1200 participants (300 participants per condition).

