Analyses will be conducted on the intention-to-treat (ITT) sample: all randomized participants will be included in the analyses regardless of their adherence and completion of the intervention. Per-protocol analyses in the sample of those participants who provide responses posttest will additionally be performed. Results of ITT and per-protocol analyses will be compared to check the robustness of the effects. Range and randomness of the missing data will be assessed with Little’s missing completely at random test [58]. Furthermore, we will conduct a dropout analysis comparing the baseline scores of those participants that remained in the study and those that dropped out, using ANOVA for continuous variables and χ^*2*^ tests for categorical variables. Dropout will be defined as those participants who did not fill out measurements beyond pretest. Missing data will be imputed by the means of multiple imputation. Because study outcomes are assessed three times, we will impute missing data using the baseline measurements as predictors, the measurements of the subsequent outcomes and the baseline covariates that could potentially be responsible for the missing data [59].

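### The stated predictors of the imputation model omit the randomised condition, so the ITT effect is pulled towards zero if the list is followed as written

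*Protocol article*

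**What the plan says.** All of the analysis text is in the protocol article, Statistical analysis.

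- Analysis set: ITT, where "all randomized participants will be included in the analyses regardless of their adherence and completion of the intervention".
- Analysis model: ANCOVA with "condition assignment as a factor, all primary and secondary measures at posttest as outcomes, and their pretest values as covariates".
- Missing data: "Missing data will be imputed by the means of multiple imputation".
- Imputation predictors: "we will impute missing data using the baseline measurements as predictors, the measurements of the subsequent outcomes and the baseline covariates". The sentence goes on to limit these covariates to ones that might account for the missingness, and cites a reference.
- Dropout: "Dropout will be defined as those participants who did not fill out measurements beyond pretest".
- An additional analysis of posttest responders is to be compared with ITT as a robustness check.

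The Sample size section warns that "a high dropout rate is usually encountered in unguided interventions", cites a range of 5 to 45%, and raises the total from 607 to 1200.

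**The concern.** Condition is the effect that every ANCOVA estimates, yet it is absent from the predictors named for imputation. An imputation model without it treats participants in different conditions as exchangeable given their other data, so the imputed values understate any difference between conditions. The analysis model then estimates a term that was left out when part of its data were generated.

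Three things are at stake. The main estimate is biased towards no difference, at dropout levels the protocol itself expects. The 6- and 12-month ANCOVAs are affected too if imputed by the same rule. And the ITT versus responder comparison, meant to show robustness, would be distorted by the rule.

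**Working it through.** **Inputs from the protocol.** Four conditions of 300, 1:1:1:1; dropout 5 to 45%; dropouts defined as having nothing after pretest; alpha 0.05 / 25 = 0.002. The planned inflation allows for 1 − 607/1200 = 49% loss.

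**The plan's own figure, and which effect sizes to use.** The text says "Taking into account the minimum effect size of *d* = 0.20". A noncentral F calculation (4 groups, 1 covariate, 3 numerator df, noncentrality N × f²) at alpha 0.002 and power 0.90 returns N = 607 when f = 0.20: noncentrality 607 × 0.04 = 24.28, power 0.9002. So 607 follows if 0.20 is Cohen's f. With two conditions at d and two at zero, f = d/2, so f = 0.20 corresponds to d = 0.40. That labelling is a separate matter; both d = 0.20 and d = 0.40 are used below.

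**No data after pretest.** Imputed values depend on baseline only, and randomisation balances baseline. The observed share (1 − m) carries d and the imputed share m carries no condition effect:

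estimate ≈ (1 − m) × d + m × 0 = d × (1 − m).

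**Simulation.** 4 × 300 participants, 300 replicates, 10 imputations by Bayesian normal regression, ANCOVA on posttest (experimental versus active control), Rubin's rules. Assumed: missingness completely at random, correlation 0.5 between time points, constant effect over time. Monte Carlo standard error is at most about 0.006.

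| True d | m | d × (1 − m) | Condition omitted | Condition included |
|---|---|---|---|---|
| 0.20 | 5% | 0.190 | 0.184 | 0.202 |
| 0.20 | 25% | 0.150 | 0.151 | 0.193 |
| 0.20 | 45% | 0.110 | 0.105 | 0.203 |
| 0.40 | 5% | 0.380 | 0.386 | 0.402 |
| 0.40 | 25% | 0.300 | 0.307 | 0.390 |
| 0.40 | 45% | 0.220 | 0.220 | 0.404 |

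The bias hardly depends on the correlation: at d = 0.40 and 45% missing, the estimate is 0.218 at r = 0.3 and 0.221 at r = 0.7. A separate set of runs (600 trials, 20 imputations, r = 0.6, monotone missingness, d = 0.20) gave 0.193, 0.146 and 0.113 at 5, 25 and 45% without condition, and 0.203, 0.195 and 0.207 with it.

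**Posttest missing, both follow-ups observed.** Later outcomes carry part of the condition effect into the imputed values. With d = 0.40 and r = 0.5, omitting condition gives 0.354 at 25% and 0.318 at 45%; including it gives 0.401 and 0.402. At 45% the loss is 0.40 − 0.318 = 0.082, against 0.40 − 0.220 = 0.180 with no later data, so a little under half as large. At r = 0.3 and r = 0.7 the 45% estimates are 0.296 and 0.330.

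**Unequal dropout.** With no later data, 45% missing in the experimental conditions and 25% in the controls, d = 0.40 becomes 0.256 without condition and 0.401 with it.

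**Power at alpha 0.002, 45% missing, no later data.** At d = 0.40: about 19% without condition, 81% with it. At d = 0.20: about 0.3% and 17%.

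**ITT versus responders.** Under the same assumptions the responder analysis is not biased by the imputation rule. At d = 0.20 and 45% missing, the expected gap from the rule alone is 0.20 − 0.11 = 0.09.

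**The case against.** The best reply is that the sentence on predictors does not say condition is excluded or that conditions are pooled. It may only explain which repeated measures and covariates will be used, the covariate set is left open with a citation, and a condensed article normally leaves the full imputation model to the SAP. It is true that a reader might infer a deliberate exclusion, and the text does not support that. What it does support is narrower. The protocol chose to name the predictors, and the one tied to the estimand is not among them. Reading condition into the baseline covariates is strained: the same section calls condition a factor or predictor and reserves the word covariate for baseline scores, and it limits the imputation covariates to those that may explain missingness.

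Four stronger readings are tempting and do not stand.

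- Shrinkage in full proportion to all missing data. This holds only for participants with nothing after pretest. The protocol does not say that people lost at posttest are mostly lost later; its definition of dropout serves the dropout analysis and does not predict a pattern.
- Near-total loss of power. The contrast of 22% with 0% at 45% missing (from the r = 0.6 runs) is specific to d = 0.20, where power is low even with condition included. At d = 0.40 the loss is serious but not total.
- Mid-intervention scores or exercise-completion data as neglected predictors of dropout. The protocol nowhere says that either predicts dropout.
- Mid-intervention scores as common auxiliary variables. They are taken only in the two experimental conditions, on scales that depend on the first module, so they cannot serve in that role.

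**Conclusion.** The point holds as a badly fixed rule. Followed as written, the listed predictors bias the ITT effect towards zero. For participants with no data after pretest the estimate is about d × (1 − m), or 45% lower at the top of the cited dropout range. Where both follow-ups are observed, the loss is roughly half that at r = 0.5 (about 20% at 45% missing posttest). The direction follows from the model. The sizes rest on missingness completely at random, an assumed correlation and a constant effect over time, none of which the protocol states. The responder analysis would expose a divergence but not its cause, so it does not repair the main analysis.

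**What to change.** State in Statistical analysis that randomised condition is included in the imputation model for every outcome and time point, or that imputation is done separately within each of the four conditions. Either keeps the imputation model consistent with the ANCOVA; in the simulations, adding condition alone recovered the true effect. The change is one sentence, made before the data are analysed, with no effect on recruitment, assessments or conduct. No further auxiliary variables are needed to settle this point.
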